Physical therapy (PT) is widely used conservative therapy in the treatment of patients with CNP and chronic musculoskeletal pain,^[16–19]^ and in particular, heat and interfering wave therapy is commonly used PT in the Republic of Korea.^[20]^ However, no studies have compared the effectiveness and safety of PDO TEA in the treatment of patients with CNP to PT. Although a previous study compared the add-on effect of PDO TEA with the usual care,^[15]^ there was no comparison with PT only, so it was difficult to examine the exact effectiveness, safety, and long-term continuous effect of TEA compared to PT, in the treatment of patients with CNP.

Therefore, based on the assumption that PDO TEA will be more effective than PT in the treatment of patients with CNP, we have planned a large-scale, randomized, controlled, and clinical trial (RCT).

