### Sample size calculation

2.3

Based on the results of a previous study and clinical significance,^[15,22]^ we assume that the mean difference (δ) between the changes in NPDS before and after intervention in each group is 11.5, and the standard deviation (SD, σ) is 20.67. We have applied a significance level of 5%, a power of 80%. As a result, a minimum of 51 participants are needed for each group. Also, considering the expected dropout rate of 20%, at least 64 subjects per group, for a total of 128 subjects, are required. 

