### Randomization and blinding

2.4

Randomization will be conducted so as not to be biased, and be blinded to subjects and researchers. Statisticians who are not involved in the conduct and evaluation of clinical trials will randomly assign 64 patients to each group with the same probability of being selected, using the statistical program SAS Version 9.4 (SAS Institute, Inc., Cary, NC). Stratified block randomization will be used. The generated randomization table will be kept by independent statisticians and the file will be protected from disclosure.

In this trial, blinding of practitioner and subject is impossible in intervention, due to the characteristics of the procedure. However, it is designed to as much as possible be assessor-blinded to control bias. Assessments will be conducted by researchers who have not performed the intervention and randomization. The assessor will ask only simple questions about the evaluation items and the contents to fill out the case report form (CRF). The assessor does not know what kind of treatment the subject is receiving.

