#### Cointerventions

2.5.3

All treatments for the improvement of CNP other than TEA or PT performed in this trial will be prohibited for all subjects. Medications that are considered to have no effect on this clinical trial (including other drugs for other diseases or AEs) will be allowed under the discretion of the researcher physician. Subjects will receive rescue medication (Acetaminophen 500 mg, up to 6 tablet per day), and will be instructed to take it only when their neck pain is so severe that it is unbearable. At each visit, the clinical research coordinator (CRC) will record on the CRF the total medication dosage (including rescue medication) used by the subject since the last visit. Subjects will be instructed to not take rescue medication from the day before assessments to the assessments of 5, 9, and 13 weeks. If a subject takes a drug without the report or judgment of a researcher, this can have a significant impact on the assessments of this clinical trial, so in this trial, the subject will be dropped.

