### Statistical analysis

2.8

All statistical analyses will be conducted as a 2-sided test, and the significance level will be set at 5%. The statistical program SAS Version 9.4 (SAS Institute Inc., Cary, NC) will be used. Multiple imputations will be used when missing values are encountered.

The data obtained from this trial will be analyzed by Full Analysis Set (FAS) and Per Protocol (PP) set. The FAS refers to the analysis method of minimizing the subjects excluded from the analysis among the randomly assigned subjects by excluding the subjects from the analysis only when there is a justifiable reason. The PP refers to the method of analyzing a group of subjects who have participated in more than 75% (3 or more TEA, 6 or more PT) of the interventions according to this clinical trial's protocol, for whom all of the assessment variables have been completely measured, and who have not violated this trial's protocol.

The descriptive statistics on the variables, such as demographic characteristics, sex, age, medical history, and drug administration will be presented for each treatment group. To verify the heterogeneity between the 2 groups at baseline, for continuous data, the mean and SD will be presented and analyzed using a Wilcoxon rank sum test or independent *t* test. The 95% confidence intervals will be provided as needed. For categorical data, frequency and percentiles will be presented and analyzed using the Fisher Exact test or Chi-square test. The primary outcome variable is the mean changes of NPDS score at 9W compared with the baseline. Analysis of covariance (ANCOVA) will be used with NPDS score at baseline as covariate and each treatment group as fixed factor. Secondary outcome variables will be analyzed in the same way as the primary outcome variables. If outcome variables are categorical variables, they will be analyzed using the Fisher Exact test or Chi-square test. The Wilcoxon signed-rank test or Paired *t* test will be used to analyze differences in measured values between pre- and post-treatment in each group. Repeated measures analysis of variance (RM-ANOVA) will be performed to examine the differences in symptom change by visit. Dunnett procedure will be used for multiple comparisons. As needed, a subgroup analysis of outcome variables such as demographic variables (age, gender, duration of illness at baseline, etc.), whether or not rescue medications were taken, and the amount of rescue medications taken can be performed.

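### The optional subgroup list includes rescue-medication use, a post-randomisation variable driven by neck pain, so TEA-PT contrasts within those strata are not randomised comparisons

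*Protocol article*

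**What the plan says.** The protocol article, section 2.8 (Statistical analysis), ends its efficacy paragraph with a permissive sentence on subgroups. It begins "As needed, a subgroup analysis of outcome variables such as demographic variables (age, gender, duration of illness at baseline, etc" and goes on to add "whether or not rescue medications were taken, and the amount of rescue medications taken can be performed". Rescue use, as yes/no and as an amount, thus stands in one list with baseline characteristics.

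Section 2.5.3 (Cointerventions) describes the rescue variable. Subjects are given acetaminophen and "will be instructed to take it only when their neck pain is so severe that it is unbearable". At each visit the coordinator "will record on the CRF the total medication dosage (including rescue medication) used by the subject since the last visit". No baseline version of the variable is defined.

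On the endpoint, section 2.8 states: "The primary outcome variable is the mean changes of NPDS score at 9W compared with the baseline". Section 2.6 says that the NPDS covers pain intensity among other domains. Section 2.4 concedes that "blinding of practitioner and subject is impossible in intervention", and the Introduction says the trial was planned "based on the assumption that PDO TEA will be more effective than PT in the treatment of patients with CNP".

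**The concern.** A subgroup factor should be fixed before treatment can influence it. Age, sex and illness duration meet that test. Rescue use does not: it accrues during the trial, and what triggers it is closely related to what the NPDS measures.

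If TEA relieves pain better than PT, fewer TEA subjects will reach the point of taking rescue. Those who still do are a more severely affected selection than the PT users. The non-users differ between arms as well, because the TEA non-users include people who would have needed rescue under PT. Unblinded subjects may also differ by arm in their readiness to take tablets.

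A contrast within either stratum then mixes the treatment effect with a difference in who is in the stratum. A reader could take the result as the effect of TEA in patients who do or do not need analgesics, which it would not be.

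**Working it through.** **Plan's own figure.** Section 2.3 assumes "the mean difference (δ) between the changes in NPDS before and after intervention in each group is 11.5", with SD 20.67, 5% significance and 80% power; section 2.8 makes tests two-sided. n per group = 2 × (1.960 + 0.842)² × 20.67² / 11.5² = 50.7, so 51. With 20% dropout, 51 / 0.80 = 63.75, so 64 per group and 128 in total. The stated sample size reproduces, and this point does not touch it.

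**Timing and cause, side by side.**
- Age, gender and duration of illness are known at baseline and cannot be altered by TEA or PT.
- Rescue use and amount are totalled since the previous visit (section 2.5.3), so they are observed after allocation. The trigger is neck pain, which both treatments aim to reduce.

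**Illustrative size.** From the document: effect d = 11.5, SD s = 20.67. Assumed, with no source in the document: rescue use p in the PT arm (20% or 40%), and the correlation r between rescue need and poor outcome (0 to 0.7).

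Model: improvement Y = d·T + s·e, where T = 1 for TEA and e is standard normal. Latent rescue need is L = −r·Y/s + √(1 − r²)·u, where u is an independent standard normal. A subject uses rescue if L > c, with c the (1 − p) normal quantile. The true effect is 11.5 for everyone, so a valid subgroup contrast would return 11.5.

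Let a = c + r·d/s, λ(x) = φ(x)/(1 − Φ(x)) and κ(x) = φ(x)/Φ(x). Then:
- Users: d − s·r·[λ(a) − λ(c)]
- Non-users: d + s·r·[κ(a) − κ(c)]
- Rescue use under TEA: 1 − Φ(a)

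Worked case, p = 40%, r = 0.7: c = 0.2533 and a = 0.2533 + 0.7 × 11.5 / 20.67 = 0.6428.
- Users: 11.5 − 14.469 × (1.2471 − 0.9659) = 7.4
- Non-users: 11.5 + 14.469 × (0.4386 − 0.6439) = 8.5
- Rescue use under TEA: 26%

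| PT rescue use | r | TEA rescue use | Users | Non-users |
|---|---|---|---|---|
| 40% | 0 | 40% | 11.5 | 11.5 |
| 40% | 0.3 | 34% | 10.8 | 10.9 |
| 40% | 0.5 | 30% | 9.4 | 9.9 |
| 40% | 0.7 | 26% | 7.4 | 8.5 |
| 20% | 0.3 | 16% | 10.7 | 11.1 |
| 20% | 0.5 | 13% | 9.2 | 10.4 |
| 20% | 0.7 | 11% | 7.0 | 9.5 |

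At 40% use the shortfall against 11.5 is about 5-6% at r = 0.3, 14-18% at 0.5 and 26-35% at 0.7. The bias is nil when r = 0. It is also nil when d = 0 and rescue is driven by pain alone, because then a = c and the two arms are selected alike.

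**Precision.** With 51 evaluable per arm and r = 0.5, there are about 20.4 PT and 15.2 TEA users. Using SD 20.67, the standard error of the user contrast is about 20.67 × √(1/20.4 + 1/15.2) = 7.0. For non-users it is about 20.67 × √(1/30.6 + 1/35.8) = 5.1. The gap between the two stratum estimates at 40% use is only about 0.2 to 1.1 points.

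**The case against.** The case on the other side has force on strength and size.

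- **The analysis is optional.** The sentence is permissive, no conclusion depends on it, and the primary full-analysis-set ANCOVA is unaffected. This stands. A reader might infer that the protocol schedules a comparison by rescue use; it only permits one.
- **The bias is conditional.** A reader might infer that such estimates are always biased. They are not: TEA must alter rescue use and rescue need must be related to outcome. The first is what the trial hopes for and the second follows from the trigger, so bias is likely, but the document does not establish it.
- **A false effect where none exists?** It is tempting to say the analysis would manufacture a difference with no NPDS effect. That takes a further assumption, that TEA lowers tablet-taking without moving the NPDS. If it cut use from 40% to 23%, the model gives false differences of about -2.3 to -5.3 points in users and -1.6 to -3.7 in non-users for r = 0.3 to 0.7. Unblinded subjects might behave so, but nothing in the document supports that shift.
- **The wording does not spell out a TEA-PT contrast within strata.** This is true, and descriptive use would be harmless. In a two-arm trial the between-arm contrast is still the natural reading.
- **Rescue use by arm may already be described.** Section 2.8 promises descriptive statistics by group that include drug administration. So it cannot be said that the protocol ignores rescue use by arm. Its absence from the secondary outcomes, and the lack of an interaction test or exploratory label, are matters of preference or of detail left to the analysis plan.

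None of this makes rescue use a valid subgroup factor. The point is not a missing detail: the protocol names the factor, and a consistent analysis plan would carry it forward.

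**Conclusion.** The point holds in limited form. Section 2.8 permits subgrouping by a variable that arises after randomisation and is triggered by the pain being treated. TEA-PT contrasts within those strata are not protected by randomisation and will be biased if TEA changes rescue use, as the trial's own hypothesis makes likely. The document fixes neither size nor direction. Under the assumed model both strata understate a uniform effect of 11.5, by nothing at r = 0 and, at 40% PT use, by up to about a third among users at r = 0.7. Those figures rest on an assumed rescue rate, correlation and normal latent model, and should be read as illustration. The bias is of the same order as, or smaller than, the sampling error of such small strata. The consequence is confined to a supportive analysis: neither the primary result nor the sample size is affected. It is a modest flaw that is nearly free to correct.

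**What to change.** In section 2.8, delete the two rescue-medication factors from the subgroup list and restrict subgroups to variables measured at baseline, such as age, gender and duration of illness. Use the dosage already collected on the CRF to compare rescue use between arms as an outcome, for example any use and total amount up to 9W. That comparison keeps the randomised groups intact and addresses the question that the subgroups were probably meant to explore.

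This is a change of analysis wording only. It needs no new data, visits or subjects and alters no rule on rescue treatment. The small cost is the loss of an optional exploratory analysis.

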### Withdrawal and dropout

2.9

During the study, if the violation of inclusion or exclusion criteria of the subject is found, or if the continuous participation of subject is difficult due to the occurrence of AEs or SAEs in the subject, the subject will be dropped from this trial under the judgment of the principal investigator. The researchers will record whether each subject participating in this trial completed it or not, and if the subject is dropped, record the reasons for stopping participation in this trial.

### Ethics and monitoring

2.10

The protocol was designed based on the *Helsinki Declaration* and the Korean Clinical Practice Guidelines, approved by the institutional review board of Daejeon University Dunsan Korean Medicine Hospital (DJDSKH-19-BM-04), and registered with the Clinical Research Information Service (identifier: KCT0003720). All subjects participating in this trial are to receive sufficient explanations for this trial, and may voluntarily decide to participate or to discontinue the trial at any time. Electronic data will be kept in a secure database to prevent personal information leakage, and documents related to research will be kept under lock and key at Daejeon University Dunsan Korean Medicine Hospital. After the study is completed, an independent researcher will edit and classify the data for statistical analysis. Monitoring of the data and performance of the trial will be conducted by a third party who is independent of this trial. The results of this trial are to be published later in a peer-reviewed paper.

## Discussion

3

This trial is designed to compare the clinical effectiveness and safety of TEA with that of PT in the treatment of patients with CNP. Although TEA treatment studies for CNP have been reported,^[14,15]^ to the best of our knowledge, no RCT investigating the effectiveness and safety of the TEA treatment compared with PT in the treatment of patients with CNP has been reported. Therefore in this trial, we will set the PT group as a control group to evaluate the differences in therapeutic effects caused by the TEA.

The researchers will diagnose the CNP of the subjects based on radiography, clinical symptoms (neck pain), medical opinion of the clinician, physical examination, etc., and then judge whether or not the subjects can participate in this trial. History taking and blood tests will be conducted, and their results can be used to exclude subjects who have hemostatic disorders, so that should prevent SAEs that could occur as a result of the TEA treatment.

However, practitioners and patients could not be blinded, because of the obvious differences in interventions. For this reason, non-specific effects that are not associated with interventions, such as placebo or treatment expectations, could occur, and it is not possible to exclude the possibility that non-specific effects will affect the outcome in favor of the TEA group. Despite these limitations, this is the first clinical trial to compare the effectiveness and safety of TEA with PT treatment in patients with CNP. Because of the RCT design of this trial, the results are expected to provide valuable data for confirming the effectiveness and safety of TEA.
